Patients will receive standard care at the discretion of the treating physicians, including all measurements and monitoring. When the treating physician chooses to give a fluid bolus (defined as 250 mL or more of fluids over 30 minutes or less), the patient will be included and the physician asked to fill out a questionnaire asking for pre-defined reasons to give fluids: hypotension, tachycardia, oliguria, low central venous pressure (CVP), high lactate levels, low mixed venous oxygen saturation (SvO_2_) or central venous oxygen saturation (ScVO_2_) and low cardiac output (CO). Also, the physician will be asked to specify what hemodynamic response of these variables is expected at completion of the bolus and one hour later. The expectations and results of the first bolus after inclusion will be measured and any further boluses given to the same patient will not lead to re-inclusion and further questionnaire’s. The first bolus after inclusion will be studied, which can be at any time during the ICU-stay. For comparison, data will be extracted from the departmental documentation system (Clinisoft^®^, TakeCare^®^ or other methods) regarding MAP, pulse rate, CO, CVP, urine output and pertinent laboratory values such as lactate, SvO_2_ or ScVO_2_ and creatinine. Measurements will be registered before the onset of the fluid bolus and until 60 min after completion of the fluid bolus. If any other static or dynamic hemodynamic variables such as Pulse Pressure Variation (PPV), Stroke Volume Variation (SVV), Extravascular Lung Water (EVLW) or Stroke Volume Index (SVI) are being measured this data will be extracted as well. Any infusions of vasoactive medications and diuretics given will also be recorded and dosages registered will be accounted for as confounders for hemodynamic changes. Any fluids administered during the study period of besides those of the fluid bolus that led to inclusion will be recorded and accounted for as confounders. Fluids will be registered as colloids, crystalloids or maintenance fluids. For MAP, pulse rate and any hemodynamic variables values will be recorded according to the sampling in the electronic system. Laboratory values will be ordered at the clinicians’ discretions as usual (usually at admission and then as indicated clinically) and extracted at these intervals. Urine output will be recorded for six hours following the fluid bolus.

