**Statistical analysis**

The accuracy of the physicians’ estimations of the effect of a fluid bolus will be described using Bland-Altman methodology. In addition, clinicians’ ability to predict the hemodynamic response will be assessed by calculating sensitivity, specificity, PPV, NPV and the area under the receiver operating characteristics curve. Outcomes will be compared after log transformation where appropriate. Comparisons will be made using t-test and ANOVA for repeated-measures or Wilcoxon signed-rank test and Kruskal-Wallis test according to the underlying distribution for continuous data and Fishers’s exact test for categorical data. Multiple regression analysis will also be performed adjusting for predefined confounding factors associated with hemodynamic changes: change in vasopressors, sedatives, diuretics, change in pacemaker rhythm, additional fluid boluses.

Ethical considerations

Ethical approval will be sought from the Ethical Review Board of Stockholm and the Austin ethical review board.

Information will be posted on the study sites, and if objections are raised to inclusion patients will not be included.

Patients in Stockholm will be covered by Sweden’s Patient Insurance policy.

Data collected will be coded and treated confidentially

The study will be observational and no changes will be made in the care of the patients included. There are no foreseeable risks for the patients to be included in this study.

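### The predefined confounder list omits change in ventilatory support and no ventilator data are specified for extraction, so its effect on CVP, blood pressure and cardiac output may be credited to the bolus

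*Protocol*

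**What the plan says.** The Statistical analysis section states: "Multiple regression analysis will also be performed adjusting for predefined confounding factors associated with hemodynamic changes". The factors follow as a plain list with no opening for additions: "change in vasopressors, sedatives, diuretics, change in pacemaker rhythm, additional fluid boluses". None concerns ventilation.

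Under Methods, the core data to be extracted are described as "regarding MAP, pulse rate, CO, CVP, urine output and pertinent laboratory values such as lactate", with venous saturation and creatinine completing the list. A further clause is open-ended but confined to hemodynamic variables: "If any other static or dynamic hemodynamic variables such as Pulse Pressure Variation (PPV), Stroke Volume Variation (SVV" and similar. Two groups of co-treatment are to be recorded as confounders. One is drugs: "Any infusions of vasoactive medications and diuretics given will also be recorded and dosages registered will be accounted for as confounders for hemodynamic changes". The other is any fluid besides the study bolus, which "will be recorded and accounted for as confounders". The time frame is: "Measurements will be registered before the onset of the fluid bolus and until 60 min after completion of the fluid bolus".

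Ventilation status, mode, PEEP and airway pressure appear nowhere in the protocol. Entry is open to adults admitted to the ICU, with no restriction by ventilation status. Changes in cardiac index, blood pressure and CVP are secondary outcomes. The primary outcome is how well clinicians' expectations match the effect seen when the bolus ends, and the planned description of that accuracy is a Bland-Altman analysis.

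**The concern.** The list is meant to hold factors associated with hemodynamic change. Airway pressure acts on venous return, and so on CVP, arterial pressure and cardiac output, which are among the variables whose change is being measured. A list specific enough to name pacemaker rhythm but silent on ventilatory support looks incomplete by its own criterion in an unrestricted ICU cohort.

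Two things are at stake. In the adjusted analysis, a CVP rise that follows a PEEP increase, or a MAP fall that follows intubation, may be read as an effect of the fluid. In the agreement analysis, the clinician's expectation would be scored against an observed change that mixes the two causes.

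This is not a detail that can simply wait for a statistical analysis plan. A later plan could add a covariate, but it could not adjust for data that were never specified for collection.

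**Working it through.** **Step 1: text check.** The three parts of the protocol, side by side:

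| Item | Named for extraction or recording (Methods) | In the regression list (Statistical analysis) |
|---|---|---|
| Vasoactive drugs / vasopressors | yes | yes |
| Diuretics | yes | yes |
| Additional fluids | yes | yes |
| Sedatives | no | yes |
| Pacemaker rhythm | no | yes |
| Ventilatory support | no | no |

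Ventilatory support is the only row absent from both columns. The rows for sedatives and pacemaker rhythm show that the Methods list is not exhaustive, so the exact statement is that ventilator data are not specified for extraction. It does not follow that they could never be obtained.

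**Step 2: exposure window.** The primary outcome is read at completion of the bolus, so its window is 30 minutes or less. The one-hour secondary outcome runs to at most 30 + 60 = 90 minutes from the start of the bolus. The opportunity for a ventilator change is smaller for the primary outcome.

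**Step 3: size, by assumption only.** The protocol gives no figure to reproduce: no event frequency, effect size or SD. Let a share p of patients have a change that moves a variable by d in one direction. Then the mean shift is p × d, the added variance is p(1 − p)d², and the SD is multiplied by √(s² + p(1 − p)d²)/s. All values of p, d and s below are assumptions, with s = 8 mmHg for MAP.

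| p | d (mmHg MAP) | Mean shift | SD factor |
|---|---|---|---|
| 0.02 | 5 | 0.1 mmHg | √(64 + 0.49)/8 = 1.004 |
| 0.10 | 5 | 0.5 mmHg | √(64 + 2.25)/8 = 1.017 |
| 0.20 | 10 | 2.0 mmHg | √(64 + 16)/8 = 1.118 |

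For CVP, a PEEP step of 5 cmH2O is 5 × 0.7356 = 3.68 mmHg. If a quarter to a half is transmitted, CVP moves by 0.92 to 1.84 mmHg in an affected patient. Over the cohort, with p from 0.10 to 0.20, the mean shift is 0.10 × 0.92 = 0.09 to 0.20 × 1.84 = 0.37 mmHg.

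**Step 4: mixed directions.** If half the affected patients move by +d and half by −d, the mean shift is zero and the added variance is p × d². With p = 0.20 and d = 10, the SD factor is √(64 + 20)/8 = 1.146. The bias disappears but the limits of agreement still widen.

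**The case against.** The strongest reply is that the regression is supplementary. The protocol says it will also be performed, and the Bland-Altman analysis is not described as adjusted, so a new covariate would leave the primary result as it is. That stands. A reader might infer that the regression is the plan's main protection against misattribution; the protocol does not give it that role. This is why the fix needs a separate agreement report as well as a covariate.

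Second, misattribution occurs only where support changes inside the window, and the documents are silent on how often. That stands too: the supportable wording is that the effect may be credited to the bolus. The low end of Step 3 is close to negligible.

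Third, changes in sedatives and vasopressors, which can accompany intubation, are already on the list and may absorb part of the effect. This is fair, but they are imperfect stand-ins for intubation and say nothing about a PEEP change made alone.

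Fourth, one pooled covariate for all ventilator changes would average effects in opposite directions and might adjust for little. That is right, and the fix below uses directional coding.

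A reader might also infer that pulse pressure variation and stroke volume variation become uninterpretable without ventilator data. The documents do not support making that a finding: both are extracted only if already being measured, neither is a named outcome, and no planned analysis uses them. The PPV in the Statistical analysis section stands beside NPV and means positive predictive value.

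**Conclusion.** The point holds in a limited form. The protocol itself fixes a closed confounder list without ventilatory support and specifies no ventilator data. Followed as written, the adjusted analysis cannot separate a change in support from the bolus in patients who have both.

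The size is unknown. The illustrations run from a mean MAP shift of 0.1 mmHg to 2.0 mmHg, and from 0.4% to 12% growth in an assumed SD of 8 mmHg, if all changes act in one direction; opposing changes shrink the bias while still widening the limits. The Background calls bolus effects small and short-lived but gives no figure, so it cannot be said that any such shift is large by comparison.

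This is a worthwhile and inexpensive improvement. It does not show that the primary result is invalid.

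**What to change.** 1. In the Methods, add to the extraction list: ventilation status or mode and PEEP at baseline, at completion and at one hour, plus any intubation or extubation in the window, taken from the same charting systems.
2. In the Statistical analysis section, add change in ventilatory support to the predefined regression list, coded with direction, for example signed change in PEEP and an intubation/extubation indicator.
3. Report the Bland-Altman agreement with and without patients who had such a change, separately at completion and at one hour, and state how many there were.

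The cost is a few more fields from charts already being read, and one or two degrees of freedom in at most 100 patients. Fewer will contribute where CO or CVP is not monitored, since monitoring is discretionary. Patient care is unaffected.

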**Preliminary results**

There are no results yet. The study is planned to be performed during fall 2017.

**Funding**

Funding will be sought from the Stockholm County Council (ALF) and external grants. A personal grant has been received for [name] (Forskar-ST).

